#### 1.4 Preliminary studies

The proposed monthly schedule of follow up will involve an extension of the period between which the child receives a health assessment by a health worker. During this time, caregivers will be asked to monitor the clinical and anthropometric status of the child at home and return to the health facility for medical attention upon development of any clinical sign of concern.

To support caregivers in these tasks, culturally-appropriate educational tools and messages, including materials for facility-based instruction (e.g. posters, pictorial flip charts), as well as for home-based use (e.g. pocket pictorial cards), were developed with MSF-France and the LASDEL in 2014. Tools covered the key topics of: a) home-based MUAC measurement; b) clinical surveillance of key danger signs or symptoms; and c) appropriate storage and distribution of the monthly therapeutic ration.

A mixed-methods pilot study of the educational tools and key messages, as well as feasibility of a monthly RUTF ration, was completed in 2015 in Madarounfa, Niger. The validity and reliability of caregiver MUAC measurements, and the retention of key messages, were assessed using standardized questionnaires administered pre- and post- intervention. Weight gain and unannounced home spot checks were used to assess home utilization of the monthly ration. Focus group discussions and semi-structured interviews with caregivers, heads of households, and health workers were used to assess the suitability of the educational tools and key messages. Results from this pilot study suggested that 1) caregivers satisfactorily retained information on clinical danger signs and the correct method to measure MUAC immediately and 28-days following a brief training and 2) the provision of a monthly ration of RUTF can be both feasible and safe, with the correct home storage and utilization of RUTF observed in the majority of households visited early in treatment, and very few cases of weight loss or hospitalization (results in press).

## 2.0 STUDY OBJECTIVES AND ENDPOINTS

The study aims to strengthen the evidence base for more flexible ways to deliver nutritional treatment in humanitarian crises.

Primary objective:

To estimate the effectiveness of monthly vs. standard weekly follow up in the treatment of uncomplicated severe acute malnutrition in children aged 6 to 59 months in terms of nutritional recovery.

Secondary objectives:

- To estimate the effectiveness of monthly vs. standard weekly follow up in the treatment of uncomplicated severe acute malnutrition in children aged 6 to 59 months in terms of hospitalization.
- To estimate the effectiveness of monthly vs. standard weekly follow up in the treatment of uncomplicated severe acute malnutrition in children aged 6 to 59 months in terms of weight gain among recovered children.
- To estimate the effect of monthly vs. standard weekly follow up in the treatment of uncomplicated severe acute malnutrition in children aged 6 to 59 months in terms of the risk of defaulting.
- To estimate the effectiveness of monthly vs. standard weekly follow up in the treatment of uncomplicated severe acute malnutrition in children aged 6 to 59 months in terms of the risk of relapse within 3 months following discharge.
- To estimate program coverage in areas receiving monthly vs. standard weekly follow up in the treatment of uncomplicated severe acute malnutrition in children aged 6 to 59.
- To assess the cost-effectiveness of monthly vs. standard weekly follow up in the treatment of uncomplicated severe acute malnutrition in children aged 6 to 59 months in terms of cost per child treated and per child recovered.

Primary endpoint:

The primary endpoint is nutritional recovery, defined by being free from medical complications, MUAC  $\geq$  125 mm, and no edema for 2 weeks if admitted with edema.

Secondary endpoints:

- Hospitalization, defined as referral to inpatient care for :

- weight/edema changes: weight loss over 3 weeks; static weight over 4 weeks; onset of edema when previously absent; persistent edema 3 weeks following admission
  - failed appetite test
  - clinical complication necessitating inpatient care: fever, hypothermia, severe dehydration, repeated vomiting, severe respiratory distress, chest in-drawing, severe pallor with respiratory distress, malaria with signs of severity, abscess or extended skin lesions, very weak, apathy or unconscious, or convulsions
- Weight gain (g / kg / day), defined as the difference in weight (g) from admission to week 4, to week 8 and to discharge divided by weight on admission (kg) and number of days between admission and week 4/week 8/discharge among recovered children.
  - Defaulting, defined as 3 missed scheduled facility visits in the weekly follow-up group and 1 missed scheduled facility visit in the monthly follow-up group.
  - Relapse, defined as maternal report of admission to any therapeutic feeding program within 3 months of discharge from the index admission.
  - Program coverage, defined as single coverage of SAM treatment, estimated in the weekly and monthly follow-up groups using the SQUEAC methodology.
  - Cost per child treated and per child recovered, defined using the societal perspective to identify all provider and caregiver costs associated with treatment.

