### 3.9 Statistical analysis

The primary outcome is nutritional recovery. Secondary outcomes include hospitalization, average daily weight gain among recovered children, defaulting, and relapse within 3 months.

All analyses will use the intention-to-treat principle and account for the stratified cluster design. We will use generalized estimating equations and robust standard errors to compare the proportion of children recovered, hospitalized, defaulted or relapsed within 3 months, and mixed effects models to compare average daily weight gain.

Interim analysis at 6 months of inclusion will be conducted to ensure the safety of children included. No adjustment will be made for multiple testing. All P values will be 2-sided, with  $P < 0.05$  considered statistically significant. Analyses will be performed using SAS version 9.3 or higher (SAS Institute Inc., Cary, NC).

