#### 4.6 Follow-up visits

At sites assigned to standard weekly follow up, follow up visits at the study sites will be scheduled every week until discharge from the nutrition program for a maximum of 12 weeks. At sites assigned to the monthly follow up, follow up visits at the study sites will be scheduled at 4, 8, 10 and 12 weeks until discharge from the nutritional program. At all follow up visits, program staff will measure appetite, weight, height/length (discharge only), MUAC, edema and conduct a clinical examination.

The child will be referred to the inpatient center during follow-up for weight/edema changes (weight loss over 3 weeks; static weight over 4 weeks; onset of edema when previously absent; persistent edema 3 weeks following admission); failed appetite test; or clinical complication necessitating inpatient care (fever, hypothermia, severe dehydration, repeated vomiting, severe respiratory distress, chest in-drawing, severe pallor with respiratory distress, malaria with signs of severity, abscess or extended skin lesions, very weak, apathy or unconscious, or convulsions). A child admitted for inpatient care will be followed on a daily basis at the hospital while receiving inpatient treatment. After stabilization, the child will resume outpatient management and study follow-up at his/her assigned outpatient facility. If the child's outpatient site was assigned to the monthly follow-up group, the child referred from inpatient care will be asked to return to the study site for outpatient management at 1, 4, 8, 10 and 12 weeks until discharge.

All caregivers will be instructed to return to the health center between scheduled visits if any clinical sign of concern develops at home. Spontaneous visits to a study health facility will be recorded with determination of the reason and treatment(s) provided.

At all follow-up visits, to understand utilization of the nutritional supplements in the household, all care givers will be asked to report average daily use of the supplement and return all finished and unfinished product.

At the discharge visit, caregivers knowledge, attitudes and practices related to the key danger signs and MUAC assessment for home-based surveillance will be assessed by standardized questionnaire (see Annex 9.2) in both the weekly and monthly follow-up groups. Compensation (e.g. 2 pieces of soap) for participation in the study will be provided to caregivers at the end of the discharge visit.

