#### 4.8 Tracing for missed visits (absences) and defaulting

We anticipate a non-negligible proportion of children will miss a scheduled visit and require tracing at home. The tracing of these children will be essential to insure complete data for a comparison of intervention groups.

To facilitate tracing of children for home visits, standard care includes notation of the child's residence (ward and area) and caregiver's name in the program registration book at admission. On a weekly basis at routine weekly meetings, program staff will inform community health worker volunteers of children who have missed scheduled visits in the previous week, and all children with a missed visit will be visited at home the following week. If the child is not present at the time of the home visit, relatives or neighbors will be contacted to collect information on vital status of the child if known.

As per standard care, and regardless of intervention assignment, all study children who have missed a scheduled visit will receive a home visit by a community health worker, who will determine vital status of the child and the reason for the missed visit. The community health worker will request the caregiver to return to the study site with the child as soon as possible for the scheduled medical and nutritional follow-up.

A child is considered as a "defaulter" after 3 consecutive missed visits in the weekly follow-up group, and after 1 missed visit in the monthly follow-up group. (e.g. maximum 3 weeks in the weekly follow-up group and maximum 4 weeks in the monthly follow-up group). No difference in the incidence/risk of complications is expected between the weekly and monthly follow-up groups due to the randomization. No difference in the detection of complications between groups is expected under the assumption that caregivers, with the educational session and take

home materials provided, will be able to detect key danger signs at home in a manner similar to that observed at a health facility.

All defaulters will be visited at home by a study community health worker, who will determine vital status of the child and the reason for defaulting.

In the event of death, the Field Investigator will interview the family to obtain the cause of death using verbal autopsy methods and efforts will be made to retrieve medical records if the deceased was admitted to hospital.

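### Hospitalization is a referral whose weight and edema triggers are checked far less often in the monthly arm, and death, the outcome least open to that bias, is not a listed endpoint

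*Protocol*

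**What the plan says.** Section 2.0 of the protocol introduces the endpoint with "Hospitalization, defined as referral to inpatient care for" and then gives three groups of triggers: a weight and edema group ("weight/edema changes: weight loss over 3 weeks; static weight over 4 weeks; onset of edema when previously absent; persistent edema 3 weeks following admission"), a failed appetite test, and a list of clinical complications. Section 4.6 repeats the same triggers for both arms. It has program staff measure weight, edema and appetite at each follow-up visit.

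Section 4.6 also sets the schedules. In the weekly arm, "follow up visits at the study sites will be scheduled every week until discharge from the nutrition program for a maximum of 12 weeks". In the monthly arm, "follow up visits at the study sites will be scheduled at 4, 8, 10 and 12 weeks until discharge from the nutritional program". There is one variant: in the monthly arm, "the child referred from inpatient care will be asked to return to the study site for outpatient management at 1, 4, 8, 10 and 12" (visit times in weeks). Section 4.5 applies the same variant to children who enter the study from inpatient care.

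Between visits, Section 5.2 has monthly-arm caregivers watch nine danger signs, including edema and lack of appetite, and measure MUAC. Section 4.7 adds one unannounced home visit in the first two weeks for all children, covering MUAC, edema, clinical condition and remaining RUTF. Neither section mentions weight.

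Section 4.8 states "No difference in the incidence/risk of complications is expected between the weekly and monthly follow-up groups due to the randomization". It then expects equal detection as well, on the assumption that trained caregivers will recognise danger signs about as well as a facility would.

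Section 3.9 lists the non-primary outcomes: "Secondary outcomes include hospitalization, average daily weight gain among recovered children, defaulting, and relapse within 3 months". Death appears neither there, nor in the endpoints of Section 2.0, nor among the outcome variables in the abstract. Section 4.8 nevertheless has vital status determined when missed visits and defaulters are traced, and cause of death obtained by verbal autopsy.

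**The concern.** A referral is recorded only if someone finds a reason to refer. Some of those reasons can be found only by weighing or examining the child, and the frequency of examination is exactly what the trial randomizes. An endpoint of this kind can fall when surveillance is reduced, even if the children are no healthier.

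This matters because Section 1.1 says a reduced schedule should be adopted only on clear evidence that it is safe. Hospitalization is the listed outcome closest to safety, and it is the one exposed to this bias. The outcome least exposed, death, is collected but has no place in the comparison. A child in either arm who dies at home without referral is counted as not hospitalized.

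**Working it through.** The plan gives no figure to reproduce here. The check is a comparison of schedules followed by one line of arithmetic.

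**Step 1. Scheduled facility visits (Section 4.6; admission = week 0, child still in treatment to week 12).**

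| | Weekly | Monthly, standard | Monthly, after inpatient care |
|---|---|---|---|
| Follow-up visits to week 12 | 12 | 4 | 5 |
| Visits by week 4 | 4 | 1 | 2 |
| Visits by week 8 | 8 | 2 | 3 |
| Pairs exactly 3 weeks apart | 10 (0–3 to 9–12) | 0 | 1 (1–4) |
| Pairs exactly 4 weeks apart | 9 | 3 (0–4, 4–8, 8–12) | 3 |

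The gaps between any two visits in the standard monthly schedule are 2, 4, 6, 8, 10 and 12 weeks.

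**Step 2. Each weight and edema trigger in the standard monthly schedule.**

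- *Weight loss over 3 weeks:* no matching pair of scheduled visits. A net loss over 4 weeks or more can be seen, and a child may be weighed at a spontaneous visit. A child whose weight at week 6 is below that at week 3, but who is above admission weight at week 4 and above the week 4 weight at week 8, meets the rule in the weekly arm and shows nothing at the monthly visits.
- *Static weight over 4 weeks:* assessable at weeks 4, 8 and 12.
- *Edema persisting at 3 weeks:* first scheduled facility check at week 4, one week later than in the weekly arm. Edema present at day 21 but gone by day 28 is an event in one arm and not in the other.
- *New edema:* assessable at any visit and at the early home visit, and taught to caregivers.

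**Step 3. Does the protocol's detection argument cover this?** Section 4.8 relies on caregivers recognising danger signs. The nine signs and MUAC in Section 5.2 do not include weight, nor do the home-visit measures in Section 4.7. The argument may hold for edema and appetite. It cannot hold for the weight rules.

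**Step 4. Direction and size.** Observed referral risk = true risk × share detected. If true risk is equal and the share detected is lower in the monthly arm, the observed monthly risk is lower. The documents give neither the referral risk nor the share of referrals due to weight or edema, so no size can be derived. The direction is not certain either, since a problem found late may lead to a later referral for a complication.

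**Step 5. Deaths.** Section 3.7 expects 3,500 children at 10 sites, so 3,500 / 2 = 1,750 per arm (5 sites × 350). Section 1.1 cites 1 to 5% mortality as general background for outpatient care.

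- 1,750 × 0.01 = 17.5, about 18
- 1,750 × 0.05 = 87.5, about 88

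Section 3.7 also prints 2,100 per group; with that figure the range would be 21 to 105.

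**The case against.** The strongest reply is that one definition applies to both arms, that referral under each schedule is a legitimate programme outcome, and that Section 2.0 presents hospitalization as an effectiveness objective, not a safety endpoint. The protocol also has other safeguards: the early home visit, spontaneous visits, adverse event reporting (Section 5.9) and an interim safety analysis at 6 months (Section 3.9). All of this is correct. As a description of programme referrals the endpoint can stay. The reply does not make it a fair between-arm measure of harm, and none of the safeguards supplies a weight or makes death a compared outcome.

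A reader might infer several stronger claims that the documents do not support:

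- *The 3-week criteria can never be applied in the monthly arm.* Persistent edema can be seen at week 4, net loss can be seen over 4 weeks, the post-inpatient schedule has one 3-week pair, and spontaneous visits are allowed.
- *Any lower monthly rate would be due only to under-detection.* That is one possible contributor, of unknown size.
- *Deaths fall outside every endpoint.* On the natural intention-to-treat reading, a child who dies before recovery counts as not recovered.
- *The protocol rests equal detection on randomization.* Section 4.8 uses randomization only for the incidence of complications; equal detection rests on training.
- *The two-week edema-free criterion for recovery fails at week 4 for the same reason.* The early home visit also checks edema, and a clear check by week 2 followed by one at week 4 spans at least two weeks.

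**Conclusion.** The concern holds in limited form. Ascertainment of hospitalization depends on visit frequency: up to 12 scheduled facility visits against 4. The 3-week weight-loss rule has ten matching visit pairs in the weekly schedule and none in the standard monthly one. The protocol's reason for expecting equal detection does not extend to weight. A lower monthly referral rate could therefore not be read as greater safety without further evidence. The size of the bias is unknown.

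The reason given in Section 4.8 for expecting equal complication risk is also wrong in itself. Randomization balances the arms at baseline; it says nothing about risk once they are under different surveillance.

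Death is recorded but not compared as death. The figure of about 18 to 88 deaths per 1,750 children assumes that the background mortality applies to this trial, which the protocol does not claim. The point should be corrected, but it concerns the safety comparison and does not invalidate the trial.

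**What to change.** 1. List all-cause death as a secondary safety endpoint, over the same period in both arms, for example enrolment to week 12, where both schedules end.
2. For the between-arm safety comparison, report inpatient admission for a clinical complication or death over that period. State that this depends less on the schedule but is not free of it, since admission still often follows a facility examination. Report weight- and edema-triggered referrals separately, as descriptive.
3. In Section 4.8, remove randomization as the reason for expecting equal complication risk.
4. The authors must reconcile the 3-week referral criteria in Sections 2.0 and 4.6 with the monthly visit schedule. No clinical rule is proposed here.

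The cost is mainly wording. Inpatient follow-up, vital status at tracing and cause of death are already planned; the authors should confirm that the case report forms, which are not shown, record the reason for each referral. There are two drawbacks. The compared endpoint will have fewer events. And for children discharged before the end of the period, vital status comes partly from the visit 3 months after discharge (Section 4.9), so the date of any death must be recorded there.

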#### 4.5 Completion of admission visit

All caregivers providing consent will be interviewed with regard to socioeconomic/household characteristics and their knowledge, attitudes and practices related to surveillance of clinical danger signs.

At sites assigned to monthly follow up, a study nurse will also provide a short educational session to caregivers describing key danger signs for which the caregiver should return to the site for clinical evaluation, instruct caregivers how to monitor changes in MUAC at home, and introduce the take-home visual aids. Educational sessions may be provided individually or in small groups as needed, with the aim of reducing the wait time of caregivers while not diminishing the quality of training provided. The assessment of caregiver knowledge, attitudes and practices related to surveillance of clinical danger signs will be repeated after the educational session. Caregiver responses to the assessment conducted after the educational session will be reviewed with caregivers to insure correct comprehension of each danger sign

for home surveillance. Caregivers will be reminded to return to the outpatient therapeutic feeding center if they believe their child's condition worsens between scheduled study visits.

Note: children transferred from inpatient to outpatient care after stabilization will be eligible for enrollment at the time of outpatient admission. These children will follow the same enrollment activities described above, but follow-up will differ in that children treated at sites assigned to the monthly follow-up group will be asked to return at 1, 4, 8, 10 and 12 weeks until discharge.

At the end of the admission visit at all sites, the caregiver and child will receive all routine medicines and nutritional treatment sufficient until the next scheduled follow-up. RUTF provided to children enrolled in the study will be marked with a unique marking to facilitate identification of RUTF specifically provided by the study. At the end of the admission visit, compensation (e.g. 2 pieces of soap) for participation in the study will be provided to caregivers.

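### Weight gain is compared at time points that the visit schedule itself determines, so identical growth would look faster in the monthly arm at weeks 4 and 8, and slower to discharge if growth decelerates

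*Protocol*

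**What the plan says.** Section 2.0 sets a secondary objective "in terms of weight gain among recovered children". The endpoint is the weight change from admission to each of three times, "divided by weight on admission (kg) and number of days between admission and week 4/week 8/discharge among recovered children". The abstract repeats this definition. Section 3.9 names average daily weight gain among recovered children as a secondary outcome, to be compared with mixed effects models.

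The discharge opportunities differ by arm (section 4.6):

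- Weekly sites: "follow up visits at the study sites will be scheduled every week until discharge from the nutrition program for a maximum of 12 weeks".
- Monthly sites: "follow up visits at the study sites will be scheduled at 4, 8, 10 and 12 weeks until discharge from the nutritional program". Children coming from inpatient care at these sites have one extra visit: "monthly follow-up group will be asked to return at 1, 4, 8, 10 and 12 weeks until discharge" (section 4.5, and likewise section 4.6).

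Recovery requires MUAC of at least 125 mm and freedom from medical complications. The only stated duration condition is "no edema for 2 weeks if admitted with edema"; no minimum stay is given for other children.

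During treatment, weight is taken at facility follow-up visits, where "program staff will measure appetite, weight, height/length (discharge only), MUAC, edema and conduct a clinical examination". These visits end at discharge. The early unannounced home visit (section 4.7) covers MUAC, edema and clinical condition but does not list weight. The next planned weight is 3 months after discharge (section 4.9).

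**The concern.** The randomized factor is the visit schedule, and the schedule decides two components of this endpoint before any child has grown differently.

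First, it decides who has a weight at the fixed times. A weekly-arm child who recovers in weeks 1 to 3 has no week-4 weight, and one who recovers in weeks 1 to 7 has no week-8 weight. In the monthly arm nearly every recovered child has a week-4 weight, and every recovered child not discharged by week 4 has a week-8 weight. Fast growers are removed from the weekly figures and kept in the monthly ones.

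Second, it decides the number of days in the gain to discharge. A monthly-arm child who reaches 125 mm in week 5 waits until week 8, and the extra days enter the denominator.

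Weight gain is one of the objectives on which monthly follow-up is to be judged effective. As defined, the trial could report better growth at weeks 4 and 8, and possibly poorer growth to discharge, with no true difference between schedules.

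**Working it through.** The protocol gives no standard deviation, expected value or power for weight gain, so there is no stated figure to reproduce. The check asks what the endpoint shows when growth is identical in both arms.

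**Inputs from the protocol.** Visits at weeks 1–12 or at weeks 4, 8, 10 and 12; discharge at the first scheduled visit with MUAC of at least 125 mm; gain = (weight at time t − admission weight) / admission weight / days; recovered children only, using weights that exist at that time.

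**Assumptions not in the protocol.** Admission MUAC about 110 mm (SD 3.5, below 115); growth scaled to cross 125 mm at a typical 4, 5.5 or 8 weeks; between-child coefficient of variation of growth 0.5; weight gain proportional to MUAC gain; growth linear, or decelerating exponentially with time constant 12, 6 or 4 weeks; no measurement noise, or MUAC noise of SD 2 mm. Each run put 200,000 children through both schedules.

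**Results without noise, weekly vs monthly (g/kg/day):**

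| Assumed growth | Week 4 | Week 8 | To discharge |
|---|---|---|---|
| Linear, 5.5 weeks | 4.76 vs 5.44 (+14%) | 3.23 vs 4.27 (+32%) | 0.0% |
| Time constant 12, 8 weeks | 4.53 vs 4.96 (+9.5%) | 3.06 vs 3.62 (+18.5%) | 4.62 vs 4.42 (−4.3%) |
| Time constant 6, 5.5 weeks | 5.46 vs 6.66 (+22%) | 3.25 vs 3.80 (+17%) | 6.52 vs 5.94 (−9%) |
| Time constant 4, 4 weeks | 6.04 vs 8.12 (+34%) | 3.37 vs 3.81 (+13%) | 8.72 vs 7.45 (−15%) |

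The third row has 77% recovery, close to the 0.80 that section 3.7 assumes for the weekly arm.

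**Why weeks 4 and 8 move.** In the third row, 72% of recovered weekly-arm children have a week-4 weight, against 100% in the monthly arm. Mean week-4 gain over all recovered children is 6.66 in both arms. The missing 28% of the weekly arm must therefore average (6.66 − 0.72 × 5.46) / 0.28 = 9.7 g/kg/day, against 5.46 in those who remain.

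At week 8 both arms have lost their faster growers, but unequally: 20% of recovered weekly-arm children contribute, against 54% in the monthly arm. The mean over all recovered children would be 5.04. The observed means are 3.25 and 3.80.

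**Why gain to discharge moves only under deceleration.** If growth is linear at rate r, the gain over d days divided by d equals r, whatever d is. If growth follows 1 − exp(−t/τ), the average rate is (1 − exp(−t/τ))/t, which falls as t grows. In the third row, mean stay is 37 days (5.29 weeks) against 46 days (6.57 weeks), with τ = 6:

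- weekly: (1 − exp(−0.881)) / 5.29 = 0.1108
- monthly: (1 − exp(−1.095)) / 6.57 = 0.1013
- ratio 0.914, that is −8.6%, close to the simulated −9%.

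Mean stay was about 7 to 10 days longer in the monthly arm in these runs.

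**Range over all the curves tried.** Week 4: about +5% to +35%, shrinking to 0–3% when few children recover before week 4. Week 8: about +11% to +44%. Discharge: −0.8% to +1.0% under linear growth, and about −3% to −20% under deceleration. The lower end comes from curves that plateau, for example 7.67 vs 6.11.

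**What drives it.** If every recovered child had a weight at weeks 4 and 8, whether or not already discharged, the arm difference would be 0.0% without noise and at most +2.3% with noise.

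**The case against.** The strongest reply is that the SAP may deal with this: covariates, random effects and missing data belong there, and section 3.9 already plans mixed effects models. That stands for the modelling detail. It does not answer the point, because the protocol itself fixes the population, the three times and the formula. Section 3.9 applies the model to the derived rate, and a model of that rate cannot supply weights that were never taken.

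A second reply is that the percentages rest on assumed growth curves. They do, and the sizes should be read as ranges. The direction at weeks 4 and 8 held under every shape tried.

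Two protocol features narrow the gap for some children: the 2-week edema-free condition and the week-1 visit for inpatient transfers. The simulation ignores both.

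Some stronger readings are tempting but not supported:

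- A reader might infer that gain to discharge is biased downward in the monthly arm in any case. That needs growth that slows during treatment, which the protocol does not state.
- A reader might infer that the recovered-only restriction is the main cause. With complete weights it moves the comparison by only about 0–2%; the driver is schedule-dependent discharge and the weights missing after it.
- A reader might infer a contradiction with "All analyses will use the intention-to-treat principle and account for the stratified cluster design". Sections 2.0 and 3.9 openly define a recovered-only endpoint, and those children can still be analysed in their assigned arm.
- A reader might infer that edema fluid in admission weight favours one arm. Nothing shows that; it affects both arms in the same way.

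**Conclusion.** The point holds for all three comparisons, with different force. At week 8 it is strongest: with identical growth the monthly arm appears about 11% to 44% faster, linear or not. At week 4 the direction is the same, at about 5% to 35%, with a size that depends on how many children recover before week 4. For gain to discharge it is conditional: about 3% to 20% lower in the monthly arm if growth decelerates, and no material difference if growth is linear.

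These figures assume that discharge happens only at scheduled visits, that weight gain tracks MUAC gain, and that the analysis uses the weights actually observed at each time. The endpoint is secondary, and the primary comparison of recovery is untouched. The definition should be changed before analysis, because as written an arm difference in weight gain cannot be separated from the effect of the schedule on who is measured and when.

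**What to change.** Make the between-arm weight comparison the gain from admission to week 4 in all enrolled children, estimated from all recorded weights.

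- Enter time as categorical visit week or as a spline, not as a straight line. With identical decelerating growth, a straight-line model of all recorded weights still left an arm difference of −9.6% to −11.4%. A quadratic term reduced the 4-week difference to between −0.2% and −3.8%.
- Use recorded follow-up MUAC, either modelled jointly with weight or in multiple imputation of week-4 weights missing after early discharge, because discharge depends on it. Estimating week-4 gain in all enrolled children from recorded weights and MUAC cut the artefact to about 1%.
- Keep the center and stratum terms.
- Keep week-8 gain and gain to discharge among recovered children as descriptive program indicators, shown with length of stay and the number contributing per arm.

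No new data and no change to care or visits are needed. The cost is an amendment to the secondary objective and endpoint wording in the abstract and sections 2.0 and 3.9. The remaining weakness is that week-4 weights of weekly-arm children discharged early would be model-based. This assumes that discharge depends on recorded measurements and that growth can be extrapolated for up to 3 weeks after discharge.
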